### Follow-up and quality of life measurements

Postoperative treatment, blood tests, and outpatient clinic visits will be according to local protocols. The patients will be sent 3 kinds of surveys: the EQ-5D-5L for quality of life evaluation, after 1 week, 4 weeks, 16 weeks, and 23 weeks postoperatively; the iMCQ, for the evaluation of medical consumption, after 23 and 26 weeks postoperatively; and the iPCQ, for the economic evaluation, after 26 weeks postoperatively. These forms can be completed online or at home by the patients and send to the investigators by post. These questionnaires will be included in the CRFs

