### Recruitment {15}

Patients scheduled to undergo open AAA repair will be informed about the study by their attending vascular surgeon in the outpatient clinic of participating hospitals about the study and the informed consent procedure will be explained. Informed consent will only be obtained by medical personnel who are GCP licensed. Also, a mandatory training by research staff has to be completed and the site initiation visit (SIV) completed {26a}. This SIV is performed by an external, independent trial research organization: Julius Clinical. A total of 750 patients with an abdominal aortic aneurysm requiring open aneurysm repair will be included in the ACTION-1 study, after signing informed consent (Fig. 1). An EQ-5D-5L questionnaire is handed out to the patient after receiving informed consent. The patient returns the form by post to the investigators, or bring the form when admitted for surgery, for baseline values. Figure 2 shows the participant timeline {13} and Fig. 3 shows the study schedule.

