## Economic evaluation

### Cost-effectiveness analysis (CEA)

General considerations: We hypothesize that ACT-guided heparinization could lower the rate of TEC and TEC-related mortality to in total 11% and that the quality of life can be increased from 73 to 76%. The economic evaluation of ACT-guided heparinization against standard care with a standardized bolus of heparin will be performed as cost-utility analyses and a cost-effectiveness analysis from a societal perspective with the costs per quality-adjusted life year (QALY) and the costs per prevented complication as the primary economic outcomes. The cost-utility analysis can be used for policy making and composition of a guideline. The cost-effectiveness analysis (CEA) relates to the clinical outcome parameter and may be used for prioritization or benchmarking of strategies that enhance surgical patient safety. The CEA and CUA will be based on a time horizon of 6 months. All related complications are within the time horizon of 6 months and patients will be recovered from the surgery. For on-going complications such as leg amputations, colostomy, permanent neurological deficits, and dialysis, a CEA and CUA with a lifelong time horizon will be made using extrapolation and model-based techniques. For this time horizon, discounting of effects and costs will be performed as stated in the most recent guidelines for cost analysis [36]. To account for uncertainties in the lifelong time horizon, a probabilistic sensitivity analysis will be performed.

Incremental cost-effectiveness ratios will be calculated as the difference in costs per QALY gained and as the difference in costs prevented complications. Sampling variability will be accounted for by bias-corrected and accelerated non-parametric bootstrapping. Results will be reported along with their 95% confidence intervals and displayed graphically with cost-effectiveness planes and with cost-effectiveness acceptability curves. One-way and multi-way sensitivity analyses will be done for the unit costs of the most common complications. Some missing data can be expected; if missing data is at random, this will be handled through multiple imputations with predictive mean matching.

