### Cost analysis

Medical costs, patient costs, and productivity losses will be included in the evaluation. The medical costs cover the costs of surgery and related complications, anesthesia, theater, perioperative materials, inpatient stay at the ICU, and the wards and medications. The patient costs include out-of-the-pocket expenses like over-the-counter medication and health care-related travel costs. Productivity losses are costs resulting from being absent and decreased productivity during work. Hospital health care utilization will be retrieved from CRFs and hospital information systems. Data on out-of-hospital health care will be gathered with the iMTA Medical Consumption Questionnaire (iMCQ) adjusted to the study setting. The productivity losses will be documented with the iMTA Productivity Cost Questionnaire (iPCQ). Questions on out-of-pocket expenses will be added to these patient questionnaires. Costs will be price indexed based on consumer price indices (CPI).

Costs will be calculated for individual patients as the product sum of the resource use and the respective unit costs. The iMCQ questionnaire will be sent 13 and 26 weeks after surgery, and the iPCQ only 26 weeks after surgery.

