### Patient outcome analysis

Patients will be asked to complete the EQ-5D-5L health status questionnaire at baseline, 1 week, 4 weeks, 13weeks, and 26 weeks after surgery. These forms can be completed online or at home by the patients and send to the investigators by post. These questionnaires will be included in the CRFs. The EQ-5D-5L scoring profiles can be converted into a health utility score based on general population-based Dutch tariffs [37]. QALYs will be calculated for each patient using linear interpolation between the successive health utility assessments over time.

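### The follow-up section and the economic sections give different questionnaire weeks, and the follow-up version leaves utilities three weeks short of the 6-month horizon

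*Protocol article*

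**What the plan says.** **Follow-up and quality of life measurements** lists three postoperative mailings. The times for the first two, beginning with the EQ-5D-5L, read: "after 1 week, 4 weeks, 16 weeks, and 23 weeks postoperatively; the iMCQ, for the evaluation of medical consumption, after 23 and 26 weeks". The third form, the iPCQ, goes out once, at week 26.

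**Patient outcome analysis** has the EQ-5D-5L completed "at baseline, 1 week, 4 weeks, 13weeks, and 26 weeks after surgery". It derives each patient's QALYs by linear interpolation from one utility measurement to the next.

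**Cost analysis** says: "The iMCQ questionnaire will be sent 13 and 26 weeks after surgery, and the iPCQ only 26 weeks after surgery". It uses the iMCQ, adapted to the study, for care outside hospital. Hospital use comes from the case report forms and hospital systems.

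**Cost-effectiveness analysis (CEA)** sets the period: "The CEA and CUA will be based on a time horizon of 6 months". It names cost per QALY as one of two primary economic outcomes, the other being cost per complication prevented.

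**Recruitment** supplies the baseline measurement: "An EQ-5D-5L questionnaire is handed out to the patient after receiving informed consent".

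**The concern.** Both timetables are in the current text, in running prose, and neither is marked as superseded. They cannot both be followed. The economic analysis needs utilities and resource use over six months, and it states an interpolation method that works only between observed points. A schedule that stops measuring utility before week 26, or that places both consumption forms near the end, fits that analysis poorly.

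At stake are the QALY estimate and the out-of-hospital part of the cost estimate. A measurement not taken at its time cannot be collected later; it can only be imputed. Trial status reports 90 patients enrolled of the 750 planned, so 660 (88%) were still to come when the article was written, and a correction would reach most of the trial.

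**Working it through.** The plan gives no figure of its own to reproduce here. The check compares the sections and counts the weeks that each schedule covers, taking 6 months as 26 weeks.

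**1. Side by side**

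| Instrument | Follow-up section | Economic sections | Agree? |
|---|---|---|---|
| EQ-5D-5L, baseline | not listed (postoperative mailings only) | yes | yes, through Recruitment |
| EQ-5D-5L, postoperative weeks | 1, 4, 16, 23 | 1, 4, 13, 26 | on 1 and 4 only |
| iMCQ, weeks | 23, 26 | 13, 26 | on 26 only |
| iPCQ, week | 26 | 26 | yes |

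Two of the four postoperative EQ-5D-5L times and one of the two iMCQ times conflict.

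**2. Utilities**

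Interpolation reaches only as far as the last assessment.

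- Economic sections: 26 of 26 weeks.
- Follow-up section: 23 of 26 weeks. Uncovered: 26 − 23 = 3 weeks; 3/26 = 11.5%.

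For scale, take the quality-of-life values of 73% and 76% in the CEA section as constant utilities:

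- Uncovered part: 0.73 × 3/52 = 0.042 and 0.76 × 3/52 = 0.044 QALY.
- Full horizon: 0.73 × 26/52 = 0.365 and 0.76 × 26/52 = 0.380 QALY.
- A constant gain of 0.03: 0.03 × 26/52 = 0.0150 QALY over 26 weeks, but 0.03 × 23/52 = 0.0133 if counting stops at week 23.

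Suppose instead that the week-23 value is carried forward. Assume, for illustration only, utilities of 0.73, 0.30, 0.60, 0.70 and 0.76 at weeks 0, 1, 4, 13 and 26, joined by straight lines. The area is 0.3309 QALY on the economic schedule. On the follow-up schedule with week 23 carried forward it is 0.3288, a difference of 0.0021/0.3309 = 0.6%. With 0.50 at week 1 the figures are 0.3386 and 0.3365, again 0.6%.

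**3. Out-of-hospital care**

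The recall period is not stated, so it is varied as an assumption. A form at week t with recall r covers weeks max(0, t − r) to t, and coverage is the union over the two forms.

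| Assumed recall | Follow-up section (23, 26) | Weeks covered | Cost analysis (13, 26) | Weeks covered |
|---|---|---|---|---|
| 4 weeks | 19–23, 22–26 | 7 | 9–13, 22–26 | 8 |
| 13 weeks | 10–23, 13–26 | 16 | 0–13, 13–26 | 26 |
| 23 weeks | 0–23, 3–26 | 26 | 0–13, 3–26 | 26 |
| 26 weeks | 0–23, 0–26 | 26 | 0–13, 0–26 | 26 |
| since the previous form | 0–23, 23–26 | 26 | 0–13, 13–26 | 26 |

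With 13-week recall, the spacing that divides the horizon into two equal halves, the follow-up schedule never asks about weeks 0–10 (10/26 = 38%) and asks about weeks 13–23 twice. For any fixed recall below 23 weeks it leaves some early weeks unasked.

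**The case against.** The strongest reply is that this is a slip of the pen. Exchanging the final digits of 13 and 26 gives 16 and 23, and the iMCQ pair differs by one digit. The economic sections agree with each other and with the horizon, and the publication section also refers to six-month surveys. The intended schedule can therefore be inferred. The article condenses a fuller protocol, and its schedule figure is not visible here. This argument stands as to the likely origin and lowers the severity. It does not remove the error, because the section that tells readers when forms are sent is the one that does not fit the analysis.

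A reader might infer four stronger things that the document does not support.

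- **That the follow-up schedule cannot support a 6-month analysis.** It covers 23 of 26 weeks, and carrying the last value forward changes the illustrative totals by under 1%. What is missing is a stated rule.
- **That early cost data would be lost, including the cost of complications.** The loss depends on recall. It is nil at 23 weeks or more or when each form asks about the time since the last, and at 4 weeks the two schedules differ by a single week. Hospital costs do not come from the iMCQ, and the thrombo-embolic events are counted within 30 days or the same admission, so much of their cost is captured elsewhere.
- **That sites follow different schedules and comparability is broken.** Nothing shows this. Forms are returned to the investigators and held in one database. Randomization is stratified by center, so both arms at a site would be expected to share a schedule.
- **That the follow-up section drops the baseline form.** Recruitment provides it.

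**Conclusion.** The contradiction is real and should be corrected. Only the schedule in the economic sections reaches the 6-month horizon under the stated interpolation. The follow-up version leaves 3 of 26 weeks (11.5%) without a closing utility.

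The effect on out-of-hospital costs is conditional. It ranges from no loss to 10 weeks more left unasked than under the Cost analysis schedule (16 against 26 weeks covered) across the recall periods tried, and the document does not say which applies. Nor does it show which schedule patients were actually sent.

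Severity is moderate. The point concerns secondary quality-of-life and economic outcomes, including cost per QALY. The primary efficacy and safety endpoints, the sample size and hospital costs are untouched.

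**What to change.** 1. Correct the follow-up section to the schedule of the economic analysis: EQ-5D-5L at baseline, 1, 4, 13 and 26 weeks; iMCQ at 13 and 26 weeks; iPCQ at 26 weeks.
2. Check which schedule the eCRF or mail-out has used for the patients enrolled so far.
3. Where week-16 and week-23 EQ-5D-5L forms were sent, interpolate on actual completion dates and state in advance how the interval to week 26 is filled.
4. State the iMCQ recall period, so that coverage of the 26 weeks, and any period asked about twice, can be seen and handled.

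The cost is a corrected sentence, a check of the mail-out settings and a short analysis rule. No forms are added.

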### Data collection and management {18 a,b, 19}

After 30 days, all postoperative variables will be collected into the electronic database. All study parameters are standard care and can be reproduced from electronic patient files. Extensive standard operating procedures (SOP) are present to secure that data is properly scored.

All data will be collected at each participating center using the eCRF in the electronic database Castor EDC. Castor complies with all applicable laws and regulations with regard to ICHG GCP and the General Data Protection Regulation (GDPR). Each participating center will maintain a key list. This key list stays in the local hospital and will not be shared. After completion of the study, all study documents will be stored on site for 25 years.

All participating sites will be monitored by a Clinical Research Associate (CRA) of the sponsor Dijklander ziekenhuis and a selection site by a monitor of Julius Clinical, a Clinical Research Organization (CRO) {27}.

After completion of the trial, all raw data will be made available for others, following the mandatory policy of ZonMw. No contractual agreements are made that limit any access for other investigators {29}.

### Statistical analysis {20 a,b,c}

Descriptive statistics of continuous variables will be presented as means with standard deviations (SD) or medians with inter-quartile ranges (IQR) depending on the distribution of the data.

Categorical data will be presented as proportions and numbers. The statistical efficacy analysis will be conducted according to the intention-to-treat principle. A separate per-protocol analysis will be performed additionally as a sensitivity analysis. All analyses will be performed with the latest version of the Statistical Package for Social Sciences (SPSS, SPSS Inc., Armonk, NY, USA).

The analysis of primary efficacy and safety outcomes will be performed on an intention-to-treat basis and in a hierarchical fashion. If the statistical analysis shows that there is a statistically significant difference in the primary efficacy endpoint, a statistical analysis of the primary safety study parameter will be performed. If there is no significant difference between study groups in primary efficacy endpoint, assessment of primary safety endpoint will be considered exploratory. Subjects with missing data will be excluded per analysis.

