### Sample size calculation {14}

In the DSAA (2014 to 2016), the rate of serious complications was 29% for all patients. According to the Society for Vascular Surgery AAA 2018 guidelines, the incidence of TEC is between 15 and 36%. In our preliminary MANCO trial, the incidence of TEC was 14%. For our power calculation, the incidence of TEC is set at 14%. The vast majority of mortality after open AAA repair stems from TEC. A mortality rate of 5% after open AAA repair is derived from DSAA. The hypothesis is that a decrease of TEC will result in a lower mortality of 3%. Bleeding complications derived from the literature and from our MANCO trial and ACTION pilot study are 18–39% (scored according to E-CABG classification) [30].

Derived from data from our pilot study and from literature, the hypothesis is that ACT-guided heparinization will lower the rate of TEC to 8%. The expected incidence for the combined endpoint of TEC and mortality is therefore set at 19% for the 5000 IU group and 11% for the ACT-guided group. Using a continuity corrected chi-square test with a two-sided alpha of 5%, 337 patients are needed in each group to achieve a power of 80%. Including a dropout of 10%, a total of 750 patients are needed for the combined primary endpoints of TEC and mortality.

In our pilot study, no increase in bleeding complications was found for open AAA repair (E-CABG class 1 bleeding was 39% versus 36%). Nevertheless, it is important that excessive bleeding does not occur in the intervention group. Therefore, a non-inferiority calculation was performed. Bleeding complications and TEC are different and have a different impact on patients. Bleeding complications grade 1 E-CABG have less impact on mortality and quality of life than TEC. The expectation is an improvement in combined TEC and mortality of 8%, and the non-inferiority for bleeding complications is set at 11%.

Expecting 32% bleeding complications in the standard group and 33% in the intervention group and a non-inferiority limit of 43% (11% limit difference) with a power of 80% and a one-sided alpha of 5%, 272 patients are required in each group. Therefore, the 750 patients which are needed for the combined primary endpoints of TEC and mortality are sufficient to also evaluate the non-inferiority for bleeding complications.

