#### 5000 IU of heparin

A single dose of 5000 IU of heparin is given 3–5 min before clamping of the aorta. No ACT measurements are performed. Only on clarified indications, extra doses of heparin or protamine are permitted, at the discretion of the attending vascular surgeon. Deviations from the protocol will be clearly stated with reasoning in the operative report.

Patients with additional doses of heparin or protamine outside the protocol will not be excluded from the trial. Evaluation will be performed according to intention-to-treat analysis but also a per-protocol analysis will be performed and, if indicated, a sensitivity analysis.

In the intention-to-treat analysis, all patients who were randomised and meet the inclusion and exclusion criteria will be included.

A per-protocol analysis will be performed on the patients who fulfill the following:

ACT group:
Patients who received a starting dose of 100 IU/kg and reached an ACT ≥200 s within 30 min after cross clamping of the aorta with or without additional heparin dosages

and
2.Received extra dosage(s) of heparin in case ACT dropped below 200 s during cross clamping (noncompliance in case of restoration of arterial blood flow within 10 min is allowed)3.ACT at the end of surgery was <180 s with or without administration of protamine

5000 IU group:

The patient received a start dose of 5000 IU of heparin.

Patients will be excluded from the per-protocol analysis if:

ACT group:
Patients who did not receive a starting dose of heparin of 100 IU/kgPatients who did not reach an ACT > 200 s within 30 min after cross clamping of the aortaPatients who received extra heparin despite ACT > 200 s during cross clampingPatients who received protamine despite ACT < 180 after restoration of arterial blood flowPatients where the administered dose of heparin or protamine deviates from the directions in the protocol with more than 50% (upper or lower)

5000 IU group:
Patients who did not receive a starting dose of heparin 5000 IU

Patients will not be transferred to the other group.

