### Primary safety study parameter

Incidence of bleeding complications according to E-CABG classification, grade 1 and higher [31]. For the bleeding complications, a non-inferiority test will be used. We test the hypothesis that the difference in bleeding between the intervention group and the control group is below the a priori specified boundary of 11%. This will be tested using a one-sided *t* test with an alpha of 0.025, with the null hypothesis that the number of bleedings is above the threshold margin and the alternative hypothesis that is below the threshold margin. If the confidence interval for the bleeding complications does not include the non-inferiority limit in the per-protocol analysis and in the intention-to-treat analysis, non-inferiority for bleeding complications is established.

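### Bleeding non-inferiority is placed on intention-to-treat in one section but requires both intention-to-treat and per-protocol in another, and the stated sample size reflects only a single-set test

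*Protocol article*

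**What the plan says.** Statistical analysis {20 a,b,c} first deals with efficacy: "The statistical efficacy analysis will be conducted according to the intention-to-treat principle". The next sentence adds: "A separate per-protocol analysis will be performed additionally as a sensitivity analysis". The following paragraph names both primary outcomes: "The analysis of primary efficacy and safety outcomes will be performed on an intention-to-treat basis and in a hierarchical fashion". Bleeding is tested confirmatorily only if efficacy is significant.

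Primary safety study parameter sets an 11-point limit and a one-sided alpha of 0.025. It accepts non-inferiority only if the confidence interval leaves out the limit "in the per-protocol analysis and in the intention-to-treat analysis, non-inferiority for bleeding complications is established".

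The section 5000 IU of heparin, which also defines the per-protocol set, says: "Evaluation will be performed according to intention-to-treat analysis but also a per-protocol analysis will be performed and, if indicated, a sensitivity analysis". The ACT arm must meet several dosing and ACT conditions to count as per-protocol. The control arm must meet one, the starting dose.

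Sample size calculation {14} sizes bleeding as one comparison of 32% with 33%, "with a power of 80% and a one-sided alpha of 5%, 272 patients are required in each group", and concludes that the 750 patients "are sufficient to also evaluate the non-inferiority for bleeding complications".

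**The concern.** The same endpoint is given two deciding populations. The general section puts the safety outcome on intention-to-treat, so per-protocol has no part in the decision. The safety section makes the per-protocol result a necessary condition. If the two sets disagree, a reader can cite either section, and the choice could be made with both results in view. Part of the trial's headline claim is at stake, because the abstract requires the efficacy gain to come without more major bleeding.

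The sufficiency statement has a related gap. It allows for 10% dropout, but not for per-protocol exclusions or for having to pass two tests. The power behind it is therefore not the power of the two-set rule.

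**Working it through.** **Inputs from the article.** Bleeding 32% (control) and 33% (ACT), margin 11 points; one-sided alpha 5% for sizing and 0.025 for the planned test; 337 per group before and 750 in total after 10% dropout. I take 375 per arm, assuming 1:1 allocation.

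**Assumed.** 10%, 20%, 30% or 40% of the ACT arm and 2% of controls fall outside the per-protocol set, with the same bleeding rates inside and outside it.

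**1. The article's own figures.** n = (z_alpha + z_beta)² × [0.32×0.68 + 0.33×0.67] / (0.11 − 0.01)².
- One-sided 0.05: (1.645 + 0.842)² × 0.4387 / 0.01 = 271.2, so 272. This matches the article.
- One-sided 0.025: (1.960 + 0.842)² × 0.4387 / 0.01 = 344.3, so 345.
- The efficacy figure of 337 per group also reproduces (19% vs 11%, continuity-corrected), and 674/0.90 = 749, planned as 750.

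**2. Power of intention-to-treat alone.** Power = Φ(0.10/√(0.4387/n) − z_alpha).
- n = 337: 0.10/0.03608 = 2.772. Power is Φ(1.127) = 87.0% at 0.05 and Φ(0.812) = 79.2% at 0.025.
- n = 375: 0.10/0.03420 = 2.924. Power is Φ(1.279) = 90.0% at 0.05 and Φ(0.964) = 83.2% at 0.025.

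**3. The two statements can give opposite answers.** The upper limit is the difference + 1.96 × √(p₁(1−p₁)/n₁ + p₂(1−p₂)/n₂).
- Intention-to-treat, 131/375 vs 118/375: 0.0347 + 1.96 × 0.0344 = 10.2%. Passes.
- Per-protocol subset, 94/262 vs 116/370: 0.0453 + 1.96 × 0.0382 = 12.0%. Fails.

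The subset is nested in the full data: it leaves out 37/113 in the ACT arm and 2/5 controls.

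**4. How often, and at what cost in power.** Simulation of nested sets, 200,000 trials per scenario, Wald limits. Each cell gives power to pass both sets; in brackets, the share of trials where intention-to-treat passes and per-protocol fails.

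| Alpha, n per arm | 10% ACT loss | 20% | 30% | 40% |
|---|---|---|---|---|
| 0.025, 337 | 74.7% (4.6%) | 71.7% (7.5%) | 68.4% (10.9%) | 63.8% (15.4%) |
| 0.025, 375 | 79.4% (4.1%) | 76.4% (7.0%) | 73.0% (10.3%) | 69.0% (14.2%) |
| 0.05, 337 | 83.8% (3.5%) | 81.1% (5.9%) | 78.3% (8.8%) | 75.0% (12.1%) |
| 0.05, 375 | 87.2% (2.9%) | 85.1% (5.0%) | 82.4% (7.8%) | 79.1% (11.0%) |

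The figures concern the bleeding comparison itself, whether or not the efficacy gate is passed.

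**5. Separating the two sources of lost power.** With 375 per arm, moving from 0.05 to 0.025 takes intention-to-treat alone from 90.0% to 83.2%, about 7 points. The second set then takes a further 4 to 14 points. With 337 per arm, the alpha change takes 87.0% to 79.2%, about 8 points, and the second set a further 5 to 15. By construction, the loss from the second set equals the bracketed share.

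**The case against.** The strongest reply is that the safety section is the specific, stricter and prespecified rule. It is the only place that says when non-inferiority is established; the general section gives a basis and a testing order, but no criterion. That is a sensible way to resolve the conflict, and the fix adopts it. It remains a reader's inference, because the general section names the safety outcome itself and neither section claims precedence.

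A reader might infer three stronger points, which the article does not support.
- **That per-protocol is declared a mere sensitivity analysis for bleeding.** That sentence directly follows one about efficacy, so extending it to safety is inference. The explicit conflict is between an intention-to-treat basis and a both-sets condition.
- **That the section 5000 IU of heparin makes per-protocol optional.** Only the further sensitivity analysis is conditional there; the per-protocol analysis will be done. That section fits the two-set rule.
- **That 750 patients suffice only for a single-set test.** At the sizing alpha of 5% there is slack. Two-set power stays at 80% or more up to an ACT-arm loss somewhere between 20% and 30% with 337 per arm, or between 30% and 40% with 375.

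The larger assumed losses can also be challenged. The Discussion expects non-adherence from surgeons' reluctance to be infrequent and balanced between arms. Randomisation takes place just before surgery and bleeding is scored in hospital, so the full 10% dropout on top of per-protocol exclusions may be pessimistic. This makes the high-loss and 337-per-arm rows the less favourable end of the range. Against that, the ACT arm has several per-protocol conditions and the control arm one, so unequal losses are plausible.

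**Conclusion.** The point holds as an inconsistency in the decision rule, with a qualification to the sufficiency claim. Data that pass intention-to-treat and fail per-protocol have no single agreed reading. If intention-to-treat fails, both readings fail. Requiring both sets costs power but does not inflate type I error.

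At one-sided 0.025 the split arises in about 4% to 15% of trials, and two-set power is below 80% in every scenario tried. With 375 per arm and 10% ACT-arm loss it is within one point of 80%. These results rest on the planning rates, the assumed losses, and equal bleeding rates in excluded patients.

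No stated sample size is arithmetically wrong, and the figures do not show that 750 patients are too few. Part of the shortfall comes from sizing at 0.05 and testing at 0.025, which is a separate matter: with 337 per arm, intention-to-treat alone is already at 79%.

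**What to change.** - **Statistical analysis {20 a,b,c}:** limit the intention-to-treat-only statement to the efficacy endpoint. State that bleeding non-inferiority is decided on both sets, as in Primary safety study parameter, with per-protocol a required condition.
- **Sample size calculation {14}:** say that 272 per group is a single-set figure at one-sided 5%. Replace the unqualified sufficiency claim with the power of the two-set rule at the alpha actually used, over a stated range of per-protocol retention. Show the part due to the alpha difference separately.

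The cost is wording and one recalculation, with no added patients. The stated bleeding power becomes less favourable.
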